## Abstract

**Introduction:**

In low-income and middle-income countries in Southeast Asia, the burden of diseases among rural population remains poorly understood, posing a challenge for effective healthcare prioritisation and resource allocation. Addressing this knowledge gap, the South and Southeast Asia Community-based Trials Network (SEACTN) will undertake a survey that aims to determine the prevalence of a wide range of non-communicable and communicable diseases, as one of the key initiatives of its first project—the Rural Febrile Illness project (RFI). This survey, alongside other RFI studies that explore fever aetiology, leading causes of mortality, and establishing village and health facility maps and profiles, will provide an updated epidemiological background of the rural areas where the network is operational.

**Methods and analysis:**

During 2022–2023, a cross-sectional household survey will be conducted across three SEACTN sites in Bangladesh, Cambodia and Thailand. Using a two-stage cluster-sampling approach, we will employ a probability-proportional-to-size sample method for village, and a simple random sample for household, selection, enrolling all members from the selected households. Approximately 1500 participants will be enrolled per country. Participants will undergo questionnaire interview, physical examination and haemoglobin point-of-care testing. Blood samples will be collected and sent to central laboratories to test for chronic and acute infections, and biomarkers associated with cardiovascular disease, and diabetes. Prevalences will be presented as an overall estimate by country, and stratified and compared across sites and participants’ sociodemographic characteristics. Associations between disease status, risk factors and other characteristics will be explored.

**Ethics and dissemination:**

This study protocol has been approved by the Oxford Tropical Research Ethics Committee, National Research Ethics Committee of Bangladesh Medical Research Council, the Cambodian National Ethics Committee for Health Research, the Chiang Rai Provincial Public Health Research Ethical Committee. The results will be disseminated via the local health authorities and partners, peer-reviewed journals and conference presentations.

**Trial registration number:**

NCT05389540.

STRENGTHS AND LIMITATIONS OF THIS STUDYThe study will use diverse methods (interviews, physical examinations and laboratory tests) to gather extensive data on the prevalence, risk factors, healthcare utilisation patterns of both communicable and non-communicable diseases.The use of two-stage cluster sampling enables the sample to be representative of each study area.As an integrated component of the Rural Febrile Illness project, the findings will be synergised with outcomes of concurrent studies in these specified regions, offering a multidimensional overview of health and healthcare provision.The findings are specific to the selected rural areas and should be interpreted with caution when considering broader implications for rural populations in the study countries.

## Introduction

Life expectancy in Southeast Asia increased from 63 to 71 years between 2000 and 2019.^1^ These positive changes can be attributed, in part, to advancements in the region’s health systems, which have addressed traditional high-burden diseases, such as infectious diseases, maternal and neonatal health, and under 5 mortality.^2^ Despite these improvements, the burden of traditionally significant diseases persists, particularly in rural areas. Furthermore, there is a transition in disease epidemiology due to rapidly changing environments, growing economies and ageing populations.^3^ The shift is marked by a rising burden of non-communicable diseases and injuries, along with emerging infectious diseases (eg, COVID-19 and chikungunya).^4 5^

The knowledge of current disease epidemiology in the region, however, is limited, constraining health systems’ ability to identify healthcare priorities and direct future resource allocation.^6^ While the Global Burden of Disease study provides insights into disease burdens across countries and diseases, the accuracy of its results is impeded by the scarcity of recent epidemiological data.^6^ Given the limited coverage of disease reporting and surveillance systems in the region, research data are pivotal in bridging this information gap. Such data not only offer up-to-date information for modelling studies but are also critical for optimising resource allocation by including factors such as disease severity, the magnitude of the population affected and equity.^7^

Moreover, the marked systemic disparities in healthcare between rural and urban areas in the region highlight the need for rural-specific epidemiological data.^3^ Despite 50%–85% of the region’s population residing in rural areas, this large population group remains relatively understudied compared with countrywide estimates.^8–13^ In this context, cross-sectional surveys are an effective research method to provide timely estimates of disease prevalence in rural communities, through cost-effective approaches combining questionnaire interviews, clinical examinations and laboratory tests.

The newly formed South and Southeast Asia Community-based Trials Network (SEACTN) aims to establish a network of community-based healthcare providers and facilities capable of implementing interventions designed to triage, diagnose and treat patients within rural communities across five South and Southeast Asian countries (Bangladesh, Cambodia, Laos, Myanmar and Thailand).^14^ The first project is the Rural Febrile Illness Project (RFI), dedicated to delineating the epidemiological baseline of febrile illness in remote and underserved regions, where febrile illness and access to healthcare pose significant health challenges.^14^ RFI encompasses diverse initiatives designed to gain a multifaceted understanding of the health dynamics within these communities to effectively facilitate the identification of interventions for future studies across SEACTN. Recognising the gaps in understanding of disease prevalence, a cross-sectional household health survey has been planned as one of the key initiatives of the RFI.

This survey aims to define the prevalence of a broad spectrum of communicable and non-communicable causes of health conditions in areas where the network operates. Alongside the survey, other key initiatives of RFI include a fever aetiology study to determine the incidence, causes and outcomes of febrile illness; a verbal autopsy study to identify common causes of mortality and the circumstances surrounding death; and a village and health facility mapping study creating a detailed profile of the study villages, estimating travel time to health facilities and identifying health service provision gaps. Each initiative holds significant value as an independent study, and their results will be complementary providing a thorough comprehension of healthcare needs and enabling more equitable resource allocation.

## Methods and analysis

The SEACTN household health survey is a community-based cross-sectional survey aiming to provide an overview of the burden of disease in selected rural areas where the network is operational. The first participant was enrolled on 3 October 2022, and data collection is expected to continue until December 2023.

### Primary objectives and outcomes

To determine the prevalences of selected diseases and exposure to locally prevalent or important pathogens, including, but not limited to:IgG against selected common pathogens causing fever.Hepatitis B and C.Hepatitis B virus (HBV) surface antigen.IgG against Hepatitis C virus (HCV) and presence of HCV.Selected non-communicable diseases (eg, diabetes, raised blood cholesterol, hypertension, stroke) according to self-reported disease history, and/or physical examinations and/or laboratory tests.Self-reported illness or injury in the past 30 days.Any acute conditions (eg, fever, persistent cough, watery diarrhoea).Injury or death caused by an accident.To determine the point prevalence of different self-perceived health statuses.To determine the prevalences of major risk factors for common non-communicable diseases (eg, smoking, alcohol consumption, overweight).

### Study population and setting

All SEACTN operational areas were selected by partner organisations as they represent poor, remote and rural communities with limited access to formal healthcare.^14^ This study will be conducted in three areas, consisting of 391 villages in Bangladesh, Cambodia and Thailand (figure 1). The other sites will not take part of the study due to operational constraints.

**Figure 1 F1:**
[figure not shown]
The study sites and population of the cross-sectional household health survey conducted by the South and Southeast Asia Community-based Trials Network (SEACTN). The Bangladesh site includes 130 villages from Cox’s Bazar and Bandarban districts; the Cambodia site includes 82 villages from Battambang and Pailin provinces; and the Thailand site includes 179 villages located in Chiang Rai province. HHS, The Household Health Survey.

A two-stage cluster sampling will be used to obtain a representative sample from each study site. In the first stage, 75 villages will be selected using the probability-proportional-to-size sample method.^15–17^ For the second stage, within each village, a simple random sample of 5–7 households (adjusted to the average household size) will be selected using computer-generated random sampling from the village household list.

#### Inclusion and exclusion criteria

For each selected household, all usual household members or visitors who stayed overnight in the households before the survey are eligible to be enrolled.^18^

### Sample size

This study is adequately powered to determine the prevalences of all key indicators within each age group, with a design effect of 1.5 and a range of 5%–10% degrees of precision, while considering a maximum of 1500 participants per study country (table 1). To account for a 10% non-response rate, assuming an average household size of 4.5 persons, and enrolling all household members, the final sample size was adjusted to 1667 participants per country.^19–21^

**Table 1 T1:** Required sample size tested against the estimated prevalence of key indicators of the highest prevalence, overall and by age groups of interests

	Expected number of participants	Indicator (estimated prevalence)	Required sample size*
Overall	1500	Overweight (20%)	369
Age groups (years)			
≥15	1050	Current drinker (55%)	570
<5	150	Anaemia (30%)	122
15–49	750	Injury or death caused by recent accident (20%)	414
≥50	300	Hypertension (20%)	257

n: sample size; DEFF: design effect. Design effect of 1.5 is used to account for a slightly expected increase in variance due to clustering; N: population size; p: expected prevalence of key indicators; d: degree of precision.

*The formula used for calculating sample size is shown above. Assessing the sufficiency of the sample size for the key indicators of the highest prevalences ensures sufficient statistical power for indicators with lower prevalence. A degree of precision of 5% is applied for the sample size calculation overall and across age groups, except for the under 5 years and the 50 years or older groups, for which degrees of precision of 10% and 6% are applied, respectively.

The minimal sample size required was calculated based on the estimated prevalences of key indicators overall and within each population age group (table 1). Prevalence estimates, population proportions within each age group and average household size were derived from previously conducted national health surveys and published studies, preferably from the study country, or from countries with a similar epidemiological context.^19–29^ When the estimated prevalence of an indicator varied across study country, the highest prevalence estimates were applied.

### Study procedures

Standard operating procedures (SOPs) were developed for field procedures, sample collection and transportation. Training materials were developed and training sessions were delivered to all the study staff directly, or using a train-the-trainer model where field supervisors and managers will be trained first and then subsequently train other field staff. All research staff are experienced in community-based research or interventions. Experienced phlebotomists were recruited and trained in specimen collection and processing in the field. A monitoring and evaluation plan was devised to maximise the research quality.

#### Patient and public involvement

The potential challenges for the study include comprehensibility of the questionnaires, and willingness of selected households to participate. We have proactively addressed these concerns by involving the target population in the questionnaire validation process (section: Questionnaire interviews), and planning community mobilisation events before the survey, tailored to the local context.

Collaborators will identify contact points from local stakeholders and communities, such as village leaders, local health centre staff or community health workers, and determine the most suitable methods for establishing contact. Main events may involve community engagement meetings to explain the study purpose, organisation and procedures, and the plan for dissemination of study results. Prior to the survey day for each village, the study team will meet, or call if physical meetings are not feasible, the household head or members of the selected households. With the support of the key contact persons, this interaction will create an opportunity to address questions or concerns, enabling the survey teams to work with each community and selected household to plan an effective data collection schedule.

#### Survey schedule

On the scheduled survey day for each village, stations will be set up at a convenient location within or near the village. Household members will arrive at the survey location following their appointment to complete the procedures (figure 2). If household members do not attend the data collection at the appointment time, they will be contacted and encouraged to join the survey at another time during the day, while the research team is in the village.

**Figure 2 F2:**
[figure not shown]
Questionnaire interviews, physical examinations and laboratory procedures administrated to study participants according to age and sex.

#### Informed consent

Participants must sign the informed consent form before any study-specific procedures are performed. The informed consent will be available in the official local language. It will be presented to prospective participants by trained study staff detailing the study procedures and implications of study participation. It will be made explicit that participation is voluntary and participants are free to withdraw from the study at any time. If necessary, the informed consent process will be interpreted to dialect when participants do not speak the official local language.

Adequate time will be given to study participants to consider the information and ask questions. Written consent will then be obtained from the participants, or the caretakers of participants, in compliance with local legal age requirements, using the participant’s dated signature or thumbprint (if unable to write) and dated signature of a person who presented and obtained the informed consent. A copy of the signed informed consent document will be given to the participant. Children aged as dictated by local legislation and regulations will be required to sign the written informed assent form in addition to their parent or guardian signing a consent form.

#### Questionnaire interviews

The questionnaire consists mostly of questions adapted from well-validated and widely implemented tools (online supplemental appendix A). This approach enables direct comparison of results with previously conducted surveys by incorporating questions from the Demographic and Health Surveys, WHO STEPWise surveys for Non-communicable Disease Risk Factors (STEP) and the World Health Survey.^30–32^

10.1136/bmjopen-2023-081079.supp1Supplementary data

The questionnaire underwent adjustments and validation through pretests using behaviour coding and participant debriefing.^33 34^ During mock interviews, the observer of each interview pair recorded the interaction problems for each question, such as ‘major change in wording’, ‘question reading interrupted by the respondent’ or ‘additional prompt is provided’. All interviewers, interviewees and the observers participated in the debriefing. The pretest was conducted initially among peer researchers in English. Subsequently, the adjusted version was translated into Thai and tested among the target population in Thailand. This ensured the questionnaire’s suitability, comprehensibility and appropriate length for administration. The final questionnaire was then translated into the official languages of each study country (Bangla, Khmer and Thai) by professional translators or dedicated staff from partner organisations, and validated by the local research teams. When necessary, during face-to-face interviews, questions will be interpreted to dialect for participants who do not speak the official local language.

The questionnaire consists of four sections answered by household members based on their sex and age (figure 2, top).

The household section is completed by the household head, providing information on household characteristics and a list of all household members along with any illnesses in the past 4 weeks and health seeking behaviour.The adult section is for household members aged 15 years or older and includes questions on sociodemographic characteristics (eg, age, sex, education, marital status and occupation), disease history (eg, tuberculosis, diabetes, cardiovascular disease), self-perceived health status, health concerns, substance use (eg, tobacco and alcohol) and other disease risk factors.The women’s health section is for female household members aged 15 years or older and includes questions on contraception use, utilisation of antenatal care and delivery services.The children’s health section is answered by caretakers of children under 5 years, providing information on each child’s vaccination and breastfeeding history.

#### Physical examination

All household members will undergo weight, height and tympanic temperature measurements. Children under 5 years will also have their mid-upper arm circumference measured, and adult household members (≥15 years) will undergo blood pressure measurement (figure 2, middle). Weight will be measured with a digital scale, preferably with a taring function allowing a child’s weight to be measured while being held by an adult. Height measurements will be carried out with measuring scales/boards. Children younger than 24 months will be measured lying down on the board, while standing height will be measured for older children. Tympanic temperature will be measured with infrared thermometers.

All measures will be taken by experienced and trained staff. Consistency and comparability will be ensured by using the same validated devices previously used in studies in similar settings, whenever possible, across study sites.

#### Blood sample collection and point-of-care haemoglobin test

Blood samples will be collected from participants aged 6 months or older (figure 2, bottom). For participants aged 6 months to under 5 years, four dried blood spots (DBS) will be collected via finger or heel prick. Participants aged 5 years or older will provide venous blood samples, with 4 mL collected from those aged 5 to under 15 years, and 6 mL from participants aged 15 years or older (figure 2, bottom). After blood sample collection, appropriate samples will be tested for haemoglobin using HemoCue Hb 301 system (HemoCueAB, Ängelholm, Sweden) to detect anaemia.

The venous blood samples will be temporarily stored in cool boxes between 4°C and 8°C, for a maximum of 24 hours before centrifugation in the field laboratories. Aliquots of whole blood, serum, plasma and packed red blood cells of these samples will be stored at a minimum of −20°C or below without freeze-thaw until analysis. DBS will be air-dried in the laboratory for at least 6 hours, after which they will be placed in a plastic zip-lock bag and stored at room temperature or at 4°C or below.

#### Information, consultation and referral

On completion of the field procedures, individual participants will receive the results of their haemoglobin test and physical examinations. Participants with abnormal results will be referred to a study nurse who will provide recommendations and, if the participant wishes, further referrals in accordance with local guidelines.

#### Non-responders

Household members who fail to attend the survey (who are absent, refuse participation or for other reasons) will have their demographic characteristics (eg, sex, age) summarised from the information obtained from the household head in the household section of the questionnaire, to determine whether systematic differences exist between responders and non-responders.

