### Planned analysis

All data obtained through questionnaire interviews, physical examinations and haemoglobin point-of-care tests will be collected on tablets using an electronic data collection platform—Open Data Kit.^40^ The electronic case report form has built-in validation rules to identify missing or potentially incorrect data. Stringent checks are applied to variables used to estimate the study outcomes, such as recent fever history, diabetes history and weight. Survey interviewers cannot progress to the next question if these data are missing or outside the defined ranges. Throughout the survey, data will be continuously updated and monitored for quality. Data queries and quality reports will be generated every two to 4 weeks for data verification and correction, and to identify areas needing additional training and support, ensuring data integrity.

For descriptive summaries, means and SDs or medians with IQR for continuous variables, and proportions for categorical variables will be calculated. Outcomes will be presented as an overall estimate by country, and with 95% CIs, stratified and compared across sites and participants’ sociodemographic characteristics using appropriate tests, such as the Student’s t-test, Mann-Whitney U tests or χ^2^ tests. Associations between disease status, risk factors, self-perceived health status and other characteristics will be explored through univariate and multivariate analyses, and measures of effect will be reported with 95% CIs. Sampling weights will be accounted for, as needed, in the analysis.

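### Age and sex of absent household members are compared but not used to adjust, so overall prevalences can be biased if attendance and prevalence both vary by age or sex

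*Protocol article*

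**What the plan says.** All references are to the protocol article.

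- **Survey schedule.** Fieldwork is at stations on one day: "On the scheduled survey day for each village, stations will be set up at a convenient location within or near the village". Members who miss their appointment are "encouraged to join the survey at another time during the day, while the research team is in the village". No later visit is described.
- **Non-responders.** Absent or refusing members have their "demographic characteristics (eg, sex, age) summarised from the information obtained from the household head". The stated purpose is "to determine whether systematic differences exist between responders and non-responders". What follows if a difference is found is not stated.
- **Questionnaire interviews.** "The household section is completed by the household head", and it provides "a list of all household members along with any illnesses in the past 4 weeks and health seeking behaviour". The member list therefore exists only where the head takes part.
- **Sample size.** A 10% non-response rate raises the target from 1500 to 1667 per country.
- **Planned analysis.** Outcomes are given as an overall estimate by country, and are also stratified and compared across sites and sociodemographic groups. On weighting, the section says: "Sampling weights will be accounted for, as needed, in the analysis".
- **Discussion.** Selection and participation bias are acknowledged. The remedies named are appropriate evaluation methods, training and supporting material; no analysis step is among them.

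**The concern.** The primary objective is prevalence, and the sample is described as representative of each study area. A single station-based day can miss some groups more than others, for example people working away from the village. Several of the indicators, such as drinking, smoking and hypertension, plausibly differ by age and sex. If attendance differs along the same lines, the overall figure moves towards the groups that attend more.

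Neither safeguard named in the article deals with this. Raising 1500 to 1667 protects precision and leaves bias untouched. Sampling weights correct unequal selection, but every member of a selected household is enrolled, so all members of a household share the same selection probability. A sampling weight therefore cannot correct for which of them came.

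The cross-site comparisons are exposed too: if the age-sex pattern of attendance differs between sites, part of an unadjusted difference reflects who attended.

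**Working it through.** **1. The plan's own figure.** 1500 / (1 - 0.10) = 1666.7, rounded up to 1667. This reproduces.

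**2. Yardstick.** Current drinker, age 15 or older: p = 0.55, expected n = 1050, design effect 1.5 (Table 1).

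Standard error = sqrt(1.5 × 0.55 × 0.45 / 1050) = 1.88 points. Half-width = 1.96 × 1.88 = 3.7 points. The planned precision is 5 points.

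**3. Size of the bias in general.** Bias of the unadjusted prevalence = non-response rate × (responder minus non-responder prevalence). At 10% non-response, gaps of 5, 10, 20 and 30 points give biases of 0.5, 1, 2 and 3 points.

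**4. Two groups, at 10% non-response.** Assumptions: half the adults are men; men attend at 85% and women at 95%, so 90% overall; response is random within sex.

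- Drinking 80% in men and 30% in women (true overall 55%): (0.5 × 0.85 × 0.80 + 0.5 × 0.95 × 0.30) / 0.90 = 0.4825 / 0.90 = 53.6%. Bias -1.4 points.
- Drinking 65% and 45% (true overall 55%): (0.5 × 0.85 × 0.65 + 0.5 × 0.95 × 0.45) / 0.90 = 0.4900 / 0.90 = 54.4%. Bias -0.6 points.
- Extreme case at the same 10%, with all absence among men (80% against 100%): 52.2% and 53.9%, so biases of -2.8 and -1.1 points.
- Equal attendance in both sexes: bias 0.

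**5. Heavier absence in one group.** Assumptions: 375 men aged 15–49, 375 women aged 15–49 and 300 people aged 50 or older (the 750 and 300 are from Table 1; the even split by sex is assumed). Drinking is 80%, 40% and 42.5%, so the truth is (300 + 150 + 127.5) / 1050 = 55.0%.

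| Attendance | Respondents | Drinkers | Estimate | Bias (points) | Non-response |
|---|---|---|---|---|---|
| 70%, 97%, 97% | 917.25 | 479.175 | 52.2% | -2.8 | 12.6% |
| 60%, 97%, 97% | 879.75 | 449.175 | 51.1% | -3.9 | 16.2% |

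**6. Effect on a nominal 95% interval.** Coverage = Φ(1.96 - b/SE) - Φ(-1.96 - b/SE), with SE = 1.88 points. Biases of -0.6, -1.4, -2.8 and -3.9 points give about 94%, 89%, 69% and 45%.

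**7. What weighting does.** Multiplying each respondent by (roster count / respondent count) in the cell restores 55.0% in all these scenarios, because response was assumed random within cells. The variance factor (Kish) is (Σ share × r) × (Σ share / r), where r is the cell's attendance.

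- 85% / 95%: 0.90 × (0.5/0.85 + 0.5/0.95) = 1.003.
- 60% / 90%, a stress case with 25% non-response: 0.75 × (0.5/0.60 + 0.5/0.90) = 1.042.
- Three groups of step 5: 0.8736 × (0.3571/0.70 + 0.6429/0.97) = 1.025, and 0.8379 × (0.3571/0.60 + 0.6429/0.97) = 1.054.

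**8. What weighting leaves.** If non-responders also differ from responders by 10 points within each sex, the weighted estimate is still off by 0.10 × 10 = 1.0 point at 10% non-response, and by 0.25 × 10 = 2.5 points at 25%.

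**The case against.** The strongest objection is that the article is silent rather than wrong. The Non-responders section gives one purpose for the data and does not call it the only one. The weighting sentence neither names nor excludes a non-response factor, and the full protocol or SAP, not shown here, may contain one. This stands to the extent that nobody can say the study will make no adjustment. However, the article does state both a use for the non-responder data and a weighting approach, and neither includes a correction, although it acknowledges participation bias.

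The attendance rates and group prevalences above are all assumed, and the three-group scenarios exceed the planned 10% non-response. That also stands. At 10% with a moderate attendance gap the bias is well inside the half-width. The 55% is also the highest estimate across countries, so it need not describe each site.

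The plan does have some mitigation. Households are contacted beforehand, "enabling the survey teams to work with each community and selected household to plan an effective data collection schedule", which should reduce absence. Recent illness is reported by the head, so that outcome does not depend on each member attending.

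A reader might also infer four stronger claims that the documents do not support:

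- That age and sex are known for every non-responder. They come from the household section, so a wholly absent or refusing household has none.
- That the reported prevalences will be biased. This requires both attendance and prevalence to vary by age or sex; the article gives no attendance figures.
- That age-sex weighting would remove the bias altogether, and for free. It removes only the part explained by those variables, at a small cost in variance.
- That the roster should be taken at the pre-survey contact. The Informed consent section requires signed consent before study-specific procedures, and enrolment began in October 2022, so this would also change fieldwork under way.

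**Conclusion.** The point holds as a conditional weakness. As written, overall country prevalences and cross-site comparisons have no stated protection against attendance that differs by age and sex, although the data for a partial correction are already being collected.

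For current drinking, the bias is about -0.6 to -1.4 points at 10% non-response with a 10-point attendance gap between the sexes. It is about -3 to -4 points with heavier absence concentrated in one high-prevalence group. The expected half-width is 3.7 points. The lower end is negligible; the upper end is as large as the sampling error and would seriously reduce interval coverage. All sizes rest on assumed attendance and prevalence by group, and the bias is zero if attendance is even and non-responders resemble responders within groups. Estimates within age-sex strata are not affected by differential response across those strata.

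This is worth changing because the remedy is cheap. It is not a fatal flaw.

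**What to change.** In Planned analysis, state that overall prevalences and cross-site comparisons use design weights multiplied by a non-response adjustment within site × sex × age group, equal to roster count divided by respondent count. Compute it separately for interview and for blood-sample response, each among the people eligible for that component. Report unadjusted estimates as a sensitivity analysis.

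Report wholly non-responding households separately, by site, because they have no roster and the adjustment cannot reach them. Leave the timing of roster collection as it is.

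The change is to analysis wording only and needs no new data. The variance increase is about 0.3% to 4% in the two-group scenarios and 2.5% to 5.4% in the three-group ones. The design effect of 1.5 was set for clustering and does not include this. Any bias within age-sex cells, such as absence for work among men of the same age group, remains and should be acknowledged as a limitation.
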